#### Secondary estimand — cognitive improvement

Population: all included participantsIndividual level outcome measure: total scaled RBANS change, comparing treatment with 180 days of 400 mg oral SAMe to placeboPopulation level outcome measure: difference in means between intervention and control groups. Difference between the groups will be analyzed adjusted for baseline RBANS.

The RBANS is a multidimensional screening battery of cognitive tests useful in a variety of populations including AD, mild cognitive impairment, and other cognitive disorders (33). It has two alternate forms, and yields five index scores; Immediate Memory, Visuospatial/Constructional, Language, Attention, and Delayed Memory.

##### Intercurrent event strategy

1. Intercurrent illnesses or medication changes (including addition of sedating medications or unavailability of regular symptomatic AD medications): This estimand will be analysed in participants who undergo follow-up RBANS assessment at 180 days (+0, −10 days) and who have taken at least 80% of the study medication, and where there have been no intercurrent events blindly adjudicated as affecting cognition (principal stratum strategy)

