#### Secondary aims

Secondary aims are to determine if, compared to placebo, treatment with 400 mg oral SAMe for 180 days will 1) maintain or improve performance as measured by the Repeatable Battery for the Assessment of Neuropsychological Status (RBANS), 2) result in epigenetic changes in DNA methylation, and 3) be safe.

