### Study Estimands

#### Primary estimand

Population: all included participants.Individual level outcome measure: percentage change in plasma p-tau181 concentration (comparing baseline to 180 days). P-tau181 levels will be measured using the single-molecule array (Simoa) technique according to the manufacturer’s instructions (Quanterix Corp., US).Population level outcome measure: difference in means between intervention and control groups adjusted for baseline p-tau181 level.

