### Sample size

Allowing for potential participant attrition, the total sample size for the study is 60 (30 per arm). Sample size calculations assumed a two-tailed alpha of 0.05 and a similar baseline standard deviation between the two arms. A total sample size of 52 participants (26 per arm) would yield 80% power to observe a large treatment effect (Cohen’s d 0.8). This sample size estimation is conservative in the sense that including the baseline p-tau181 concentration in the final ANCOVA model would increase the power.

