#### Randomization

Participants will be randomized within 28 days of enrollment. The results of safety blood tests will be reviewed for clinically significant abnormalities prior to randomization. A central randomization schedule has been generated by an independent statistician who is a part of the data center at the Melbourne Brain Centre at Royal Melbourne Hospital, University of Melbourne. The randomization schedule has been programmed into an electronic case report form (eCRF) system, housed on a RedCAP platform (34, 35). Participants will be randomized in a 1:1 ratio to receive either 400 mg SAMe or matched placebo orally once per day for 180 days. Randomization will be stratified based on age at enrolment (<70 years vs ≥70 years) to minimize baseline imbalance between the treatment groups.

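### The RBANS estimand covers everyone included, but its analysis keeps only adherent, event-free participants; this post-randomisation subset is not a principal stratum and its comparison may be biased

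*Protocol article*

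**What the plan says.** All references are to the protocol article.

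- **Secondary aims:** the cognitive aim is that SAMe, compared with placebo, will "maintain or improve performance as measured by the Repeatable Battery for the Assessment of Neuropsychological Status (RBANS").
- **Secondary estimand, cognitive improvement:** the entry reads "Population: all included participants". The measure is the difference in mean RBANS change, adjusted for baseline RBANS.
- **Intercurrent event strategy under that estimand:** the events named are illnesses and medication changes, including added sedatives and loss of access to usual symptomatic AD drugs. The analysis is limited to participants with an RBANS in the 10 days up to day 180, who took 80% or more of their study medication, and "where there have been no intercurrent events blindly adjudicated as affecting cognition (principal stratum strategy").
- **Intercurrent event strategy under the primary estimand:** intercurrent events are defined as arising after randomisation. For p-tau181 the article also states a dose-response analysis regardless of compliance and a pattern mixture sensitivity analysis. Participants with COVID-19 stay in the main analysis and are removed only in a sensitivity analysis.
- **Statistical analysis:** the wider dose-response analysis is repeated, again for blood samples. Details are deferred to a separate SAP.

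The article states no corresponding inclusive analysis for RBANS.

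**The concern.** The estimand names one population and the analysis uses another. The second is selected by events after allocation, and one selection criterion is a judged effect on cognition, the construct that RBANS measures. An illness or an added sedative may follow from treatment or from cognitive decline. If so, removing those participants leaves two groups that randomisation no longer balances.

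The principal stratum label hides this. It suggests a comparison within a fixed type of participant, whereas the rule compares whoever happened to stay event-free in each arm. At stake is whether the RBANS result can be read as a randomised comparison that answers the stated aim.

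**Working it through.** **1. The plan's own figure.** The Sample size section gives a two-tailed alpha of 0.05, d = 0.8 and 26 per arm for 80% power. A two-sample t-test calculation gives 25.5, hence 26 per arm, with 80.7% power. Going from 52 to 60 allows for 8/60 = 13.3% attrition. The figures reproduce, but they concern p-tau181. No effect size or power is given for RBANS, so they do not enter below.

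**2. The two populations.** The estimand takes everyone included. The analysis removes anyone without an in-window RBANS, anyone below 80% adherence, and anyone with an adjudicated event. All three conditions become known only after randomisation, so the two statements cannot both describe the target.

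**3. The label.** A principal stratum here would be, for example, participants who would stay adherent and event-free under SAMe and also under placebo. Each participant is seen under one arm only. Event-free participants on SAMe may include people who would have had an event on placebo, and the reverse. Equating the observed subsets with the stratum needs assumptions, and none is stated.

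**4. Illustration (every input is assumed).** The outcome is in SD units, with no direct drug effect.

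- Outcome = 0.5U + e − 0.5 × (event). U is standard normal prognosis and explains 0.5² = 25% of the variance; Var(e) = 0.75.
- An event occurs when (U + noise)/√2 falls below z_p, where p is the arm's event rate. Worse prognosis therefore means more events.
- All-randomised contrast = −0.5 × (p_SAMe − p_placebo).
- Mean among event-free participants at rate p = 0.5 × (1/√2) × φ(z_p)/(1 − p) = 0.354 × φ(z_p)/(1 − p):
  - p = 0.10: 0.354 × 0.1755/0.90 = 0.069
  - p = 0.20: 0.354 × 0.2800/0.80 = 0.124
  - p = 0.30: 0.354 × 0.3477/0.70 = 0.176

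| Event rate, placebo / SAMe | All randomised | Event-free only | Gap |
|---|---|---|---|
| 15% / 15% | 0.00 | 0.00 | 0.00 |
| 20% / 10% | +0.05 | 0.069 − 0.124 = −0.055 | 0.105 |
| 10% / 20% | −0.05 | +0.055 | 0.105 |
| 30% / 10% | +0.10 | 0.069 − 0.176 = −0.107 | 0.207 |

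A simulation of the same model gave −0.054, +0.054 and −0.106 for the three unequal cases, and no difference beyond simulation noise for equal rates.

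**5. Reading the gap.** In the 20% / 10% case, 0.05 SD of the 0.105 SD gap is the direct harm of events, which the restricted analysis sets aside on purpose. That part is a change of question and not bias. The other 0.055 SD is selection. By construction the effect among people who would be event-free under both arms is zero, yet the event-free comparison shows −0.055. So in this model the restricted analysis misses the principal stratum effect as well as the effect in everyone included.

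**The case against.** The strongest defence is that the sponsor chose an efficacy question: the effect on cognition in people who take the drug and whose testing is not disturbed by other events. Adjudication is blinded, some listed events (such as unavailability of usual AD medication) may have nothing to do with treatment, and RBANS is a secondary outcome read in support of the primary. The unseen SAP may add RBANS analyses.

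Much of this stands, and it limits the point. Three stronger readings are tempting, and the documents do not support them.

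- *That the rule selects on the outcome.* It selects on illnesses and medication changes judged relevant to cognition, and not on RBANS scores.
- *That the analysis cannot answer the cognitive question.* Bias needs events that depend on both arm and prognosis. The documents neither show nor exclude this, and in the model above equal rates give no bias.
- *That the exclusions cost a known amount of power.* The d of 0.8 belongs to p-tau181, the plan already allows for attrition, and no exclusion rate is given.

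The defence does not remove the core. Blinding protects the classification of events, not their occurrence. Wanting an efficacy estimand does not turn an observed subset into a principal stratum. The SAP could add analyses, but the restriction, its label and the conflict with the stated population are fixed in the article.

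**Conclusion.** The point holds in a limited form. The stated and analysed RBANS populations disagree. The analysed set is a per-protocol subset carrying a principal stratum label without the assumptions that label needs. The resulting comparison does not estimate the effect in everyone included. It may be biased in either direction if event or adherence rates differ by arm and are related to prognosis.

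The size cannot be found from the documents. The figure of about 0.1 SD per 10-point difference in event rates is illustrative only. It rests on the assumed prognostic strength and event effect above, and about half of it is a difference in estimand and not bias.

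This is a correction that should be made to a secondary outcome. It does not touch the primary result. The 80% adherence rule is shared with the p-tau181 and epigenetic estimands; the adjudicated-event clause is specific to RBANS.

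**What to change.** - Make the RBANS analysis that matches the stated population an analysis of all randomised participants with a 180-day RBANS, in their assigned arm, adjusted for baseline RBANS, regardless of adherence, intercurrent illness or medication change. If the sponsor prefers to keep the efficacy question in front, report this analysis beside it.
- Add a missing-data sensitivity analysis like the pattern mixture model stated for the primary outcome, because requiring a 180-day RBANS still conditions on attendance.
- Keep the adherent, event-free set as a supplementary per-protocol analysis. Drop the principal stratum label unless the assumptions behind it are written down.

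This follows the article's own handling of COVID-19 for p-tau181: include in the main analysis, exclude in a sensitivity analysis.

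The cost is wording, one further model fit and the sensitivity analysis, on RBANS assessments already planned. The inclusive analysis may be somewhat noisier or diluted by transient events and non-adherence.

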#### Secondary estimand — epigenetic change

Population: all included participantsIndividual level outcome measure: DNA methylation changesPopulation level outcome measure: will be described using bioinfomatic techniques

##### Intercurrent event strategy

1. This estimand will be analysed in participants who undergo follow-up RBANS assessment at 180 days (+0, −10 days) and who have taken at least 80% of the study medication (principal stratum strategy)

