##### Intercurrent event strategy

Intercurrent events describe circumstances occurring after randomisation that preclude outcome observation or affect its interpretation. We have pre-specified possible intercurrent events and devised strategies for their handling:

Inadequate study drug adherence: Given that establishing biological efficacy is the primary objective of the trial, all participants who achieve at least 80% study medication compliance and provide a 180-day blood sample will be included in the primary efficacy analysis (principal stratum strategy). As a supplementary estimand, we will also perform a dose-response analysis in all participants who provide a blood sample within the required time period (regardless of medication compliance)COVID-19 infection: The main analysis of the primary estimand will include participants with COVID-19 infection. As a first sensitivity analysis for the primary estimand, we will perform the primary analysis excluding participants with confirmed COVID-19 infection before or during the study.Inability to collect sample for primary outcome: As a supplementary analysis for the primary estimand, the missingness at random assumption will be evaluated for any patient or system related intercurrent events preventing the collection of the primary outcome. A sensitivity analysis using a pattern mixture model will be undertaken.

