## Discussion

Present in all living cells, SAMe is the active form of the amino acid methionine. Since its structural elucidation in 1952 (44), SAMe has become recognized as the major metabolite in multiple metabolic pathways on which neuronal homeostasis depends. In the brain, SAMe is the only methyl donor for numerous reactions catalyzed by methyltransferases with substrates including DNA, neurotransmitters, signal transduction systems, and membrane phospholipids (4). SAMe’s role in transsulfuration produces glutathione, the brain’s major antioxidant (5). SAMe is required for the synthesis of the neuroregulatory polyamines spermidine and spermine, which have anti-inflammatory properties (6) and are involved in controlling cell differentiation and proliferation (7).

Clearly, SAMe’s cellular functions are of direct relevance to the prevention of neurodegeneration and its depletion, as seen in the AD central nervous system, would be expected to carry widespread deleterious sequelae. In this trial, we will explore the effect of SAMe supplementation on tau phosphorylation and epigenetics, via measurement of plasma p-tau181 and DNA methylation, respectively, in patients with AD.

Tau hyperphosphorylation: Neurofibrillary tangles comprising hyperphosphorylated tau are a hallmark of AD pathology. Tau’s degree of phosphorylation is a result of the balance between kinase and phosphatase activity. Protein phosphatase 2A (PP2A) accounts for over 70% of the brain’s phosphatase activity (45). PP2A’s stability and enzymatic activity rely on SAMe-mediated methylation of its catalytic subunit. Both the concentrations and activity of PP2A are significantly reduced in the AD brain (46, 47). Owing to diminished PP2A activity, SAMe depletion would be expected to favor the accumulation of phosphorylated tau (48).

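### The DNA-methylation estimand selects its analysis set on completing the RBANS instead of on having methylation samples

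*Protocol article*

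**What the plan says.** Under Secondary estimand — epigenetic change, the article gives DNA methylation change as the individual-level outcome and leaves the population-level summary to bioinformatic description. The intercurrent event strategy beneath it has one item: "This estimand will be analysed in participants who undergo follow-up RBANS assessment at 180 days", within a window of +0, −10 days, "and who have taken at least 80% of the study medication (principal stratum strategy"). It does not mention a baseline or follow-up sample for methylation.

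The strategy for Secondary estimand — cognitive improvement opens with the same sentence and window. It adds a further condition, that no intercurrent event was blindly adjudicated as affecting cognition.

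The primary estimand, the other one based on a biological marker, is conditioned on its own specimen: "all participants who achieve at least 80% study medication compliance and provide a 180-day blood sample will be included in the primary efficacy analysis". The Statistical analysis section repeats that rule. The Discussion presents the two markers side by side, "via measurement of plasma p-tau181 and DNA methylation, respectively, in patients with AD".

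**The concern.** An analysis set should be defined by availability of the outcome being analysed, together with whatever intercurrent event strategy has been chosen. Here the availability condition belongs to a different outcome. Nothing in the article says why a methylation result should depend on whether the participant sat the RBANS.

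Two things are at stake. First, usable paired methylation samples could be discarded in a trial of only 60 participants. Second, completing the RBANS happens after randomisation and may depend on the participant's cognitive state, which is itself a trial outcome. Selecting on it can disturb the comparability of the randomised arms for an outcome that never needed the selection. The article says the trial is run within the estimand framework in order to align objectives, endpoints and analysis. This sentence does not achieve that alignment.

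**Working it through.** **The plan's own figure.** The only related number is the sample size: "A total sample size of 52 participants (26 per arm) would yield 80% power to observe a large treatment effect (Cohen’s d 0.8). With a standardised difference of 0.8, two-sided alpha 0.05 and 80% power:

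- Normal approximation: n per arm = 2 × (1.960 + 0.842)² / 0.8² = 2 × 7.85 / 0.64 = 24.5, rounded up to 25.
- Two-sample t-test: 25.52, rounded up to 26 per arm, with power 80.7%.

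The stated 26 per arm reproduces. It concerns the primary outcome, and nothing below changes it.

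**The three rules side by side.**

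| Estimand | Outcome | Availability condition | Adherence condition | Further condition |
|---|---|---|---|---|
| Primary | Plasma p-tau181 change | 180-day blood sample | At least 80% | None in this rule |
| Cognitive improvement | RBANS change | RBANS at 180 days (+0, −10) | At least 80% | No adjudicated event affecting cognition |
| Epigenetic change | DNA methylation change | RBANS at 180 days (+0, −10) | At least 80% | None |

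In the first two rows the availability condition matches the outcome. In the third it does not. The third row is the second with the cognition-adjudication clause removed. That is what one would expect if the text was copied and only partly adapted.

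**What the rule does to adherent participants** (at least 80% of medication taken):

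| Baseline and 180-day methylation samples | In-window RBANS | Rule as written | Rule based on the sample |
|---|---|---|---|
| Yes | Yes | Analysed | Analysed |
| Yes | No | Excluded although the outcome exists | Analysed |
| No | Yes | In the set, outcome missing | Not in the set |
| No | No | Excluded | Not in the set |

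The second line carries the point: the two rules differ there in whose data are used. The third line makes little practical difference, since a participant without a methylation result contributes nothing under either rule.

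**How many fall in the second line.** This would need the joint rate of sample provision and in-window RBANS completion among adherent participants. The article gives neither rate, so the number cannot be computed.

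**The case against.** The strongest reply is that the effect will be slight. The Figure 3 legend places endpoint data collection at a single visit, within the final 10 days of treatment, and lists the RBANS in the cognitive battery. That timing agrees with the +0, −10 day window. If the methylation sample and the RBANS are taken together, the two sets largely coincide. The outcome is also secondary, its summary is descriptive, and the article says secondary results only supplement the primary evidence. All of this stands, and it limits the importance of the point. It does not make the condition right, because a participant can attend and give a sample without completing the test.

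A reader might also infer more than the article supports:

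- *That the specimen is blood.* The readable text names no methylation specimen. Blood is a reasonable assumption, but the mismatch holds for any biological sample.
- *That the losses fall on the more impaired.* This is plausible, but the article does not show it. Entry requires a Standardized Mini-Mental State score of at least 18, community living and a study partner, and follow-up is 180 days.
- *That precision suffers by a known amount.* If 10% of the set were lost, a standard error proportional to 1/√n would rise by 1/√0.9 − 1 = 5.4%. The 10% is hypothetical, and the article names no estimator for methylation to which the figure could apply.
- *That the rule contradicts the stated population of all included participants.* All four estimands pair that phrase with a narrower set, and a sample-based rule would also be narrower. It does not mark out this defect.
- *That the 80% adherence restriction should be dropped here too.* That is a separate question. The primary estimand applies the same threshold as a declared strategy, and nothing in the RBANS wording argues for changing it.

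Deferral to the statistical analysis plan is not an answer. The article states an explicit inclusion rule, so a later plan must either reproduce it or depart from it.

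**Conclusion.** The rule is wrong as written. The epigenetic estimand takes its availability condition from the RBANS estimand, and no rationale is given. Followed literally, it drops adherent participants with usable paired methylation samples because of a post-randomisation cognitive test.

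The size cannot be calculated and is probably small. That judgement assumes that methylation sampling and the RBANS both take place at the single endpoint visit. The primary p-tau181 analysis, whose rule correctly requires its own sample, is not touched. The sentence should be corrected, but the fault does not threaten the trial's main conclusion.

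**What to change.** In the intercurrent event strategy for the epigenetic estimand, replace the condition "participants who undergo follow-up RBANS assessment at 180 days" and its window with *participants who provide baseline and 180-day (+0, −10 days) samples for DNA methylation*. Keep the 80% adherence condition, so that the methylation and p-tau181 sets are defined in parallel. Carry the same wording into the statistical analysis plan, which the article says will be finalised before database lock. If the RBANS condition was intended, the sponsor should state why.

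The cost is one phrase in the estimand and the matching line in the analysis plan. No new data, visits or procedures are needed.

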#### Secondary estimand – safety

Population: all included participantsIndividual level outcome measure: presence or absence of serious adverse events (SAEs)Population level outcome measure: Difference in proportion of participants with SAEs present between the intervention and control groups

##### Intercurrent event strategy

Inadequate study drug adherence: This estimand will be analysed in participants who have taken at least 1 dose of study medication (principal stratum strategy).COVID-19 infection: COVID-19 related SAEs will be included in the analysis for this estimand, as for SAEs related to any other intercurrent events. Given the unique risk of SAEs due to the potential for increased incidence of COVID-19 over the study period, we will also perform a sensitivity analysis where COVID-19 related SAEs will be excluded from the analysis.

